### Implementation

Health care workers at the primary health care clinic identify potential participants. All individuals reporting cough are referred to the study nurse. Eligibility criteria are checked by the nurse, and subjects meeting the inclusion criteria are provided spoken and written information about the study in isiZulu and/or English; those willing to participate are taken through the informed consent process and are asked to provide a signature or thumbprint on the consent form.

A baseline assessment is performed by the study nurse. Demographic information, current symptoms, previous TB history, risk factors for drug resistance, HIV status, and history of ART use are documented on a case report form.

With both strategies, clinical decisions are made by the study nurse on the basis of the Xpert MTB/RIF result and according to pre-defined algorithms. TB patients without resistance to rifampicin are commenced on standard anti-TB therapy (4HRZE/2HR) by the study nurse. All patients with rifampicin-resistant TB are reported to the trial physician on the same day and are subsequently referred to the specialist drug-resistant TB treatment centre in Durban. Management of suspects with a negative Xpert MTB/RIF follows existing protocols for smear-negative TB suspects: oral antibiotics are prescribed and patients are advised to return if symptoms do not improve after 14 days. Patients who remain symptomatic following this course of antibiotics can be referred to the district hospital for chest X-ray and physician review. Results from MGIT culture and DST are returned through the routine laboratory system and are used to guide clinical management where appropriate.

### Outcome evaluation

To ascertain the primary and secondary outcomes, at enrolment all participants are allocated a review date 2 months from the enrolment visit. Participants are invited to attend clinic for review but are also invited to consent to telephonic follow-up and/or home visit in case clinic visit is not possible. Additional contact details are provided for at least one other family member (or other person designated by participant) at enrolment, wherever possible. Participants are told that, when attending the clinic for the follow-up visit, they will be reimbursed with a ZAR 50 grocery voucher (approximately equivalent to USD 6). Outcome data pertaining to TB treatment initiation, additional investigations, hospital attendances and admissions, and ART initiation (where appropriate) are collected on a case report form by the study nurse. In the event that no contact is made with patient or with named contact persons, follow-up information is collected from the clinic TB registers and the operational HIV programme database – permission to use these data is also included in the informed consent process.

### Statistical analysis

Analysis of baseline characteristics will be performed to characterise the study population and to identify baseline imbalances between the study arms in order to decide whether any covariates need to be adjusted for in the final analyses. The baseline data will include: age, sex, body mass index (BMI), history of previous TB, HIV infection status, CD4+ cell count, and use of antiretroviral therapy and isoniazid preventive therapy.

All final analyses will be intention-to-treat analyses performed at the individual level taking account of within-cluster correlation. The definition of TB cases for the primary outcome will be based on MGIT culture positivity. The proportion of TB cases initiated on appropriate TB treatment within 30 days will be based on whether the appropriate treatment regimen was commenced within 30 days of the initial clinic visit—appropriate regimens are defined according to drug susceptibility pattern and with reference to national guidelines (Table 1) [27]. The primary analysis will include only TB cases not on TB treatment at the time of enrolment, i.e. excluding smear non-converters or failures still on treatment. The primary outcome is a binary variable (initiation of appropriate treatment or not) so univariate logistic regression will be performed as the primary analysis using generalised estimating equations (GEE) with a binomial distribution function and a logit link [28]. The odds ratio will be reported with 95% confidence intervals and a *p*-value from the Wald test. This method will allow for the correlation between observations (within clusters) without needing to specify a distributional assumption for the correlations. In addition, important individual-level characteristics that are unbalanced between arms will be included in the model as covariates. For the secondary outcomes with binary variables, GEE models will also be fitted with a binomial distribution function and a logit link. For the secondary outcomes with time-to-event measures, Cox proportional hazard models will be fitted with the shared frailty option to account for the cluster randomisation [29]. Hazard ratios will be presented with 95% confidence intervals.

**Table 1 T1:** Definitions of appropriate initial anti-TB drug regimen for primary outcome measurement

**Case definition***	**Appropriate initial anti-TB drug regimen**
*M. tuberculosis* susceptible to rifampicin and isoniazid	Isoniazid + rifampicin + pyrazinamide + ethambutol
*M. tuberculosis* with mono-resistance to isoniazid	Isoniazid + rifampicin + pyrazinamide + ethambutol
*M. tuberculosis* with mono-resistance to rifampicin	Standardised second-line regimen§ with isoniazid
Multidrug-resistant *M. tuberculosis* (MDR-TB)†	Standardised second-line regimen§
Extensively drug-resistant *M. tuberculosis* (XDR-TB)†	Standardised XDR-TB regimenǁ

* Case definition based on results of MGIT culture + line probe assay + phenotypic DST.

† MDR-TB defined as resistance to rifampicin and isoniazid.

† XDR-TB defined as MDR plus resistance to ofloxacin and kanamycin.

§Standardised regimen according to national guidelines (kanamycin/amikacin + fluoroquinolone + ethionamide + cycloserine/terizidone ± pyrazinamide ± ethambutol) [27].

ǁStandardised regimen according to national guidelines (capreomycin + fluoroquinolone + ethionamide + cycloserine/terizidone + PAS + clofazimine) [27].

The diagnostic performance of Xpert MTB/RIF will be compared between the two arms. Estimation of sensitivity and specificity of Xpert MTB/RIF for the detection of *M. tuberculosis* against the reference standard of single MGIT culture will be based on complete case analysis (participants with paired valid Xpert MTB/RIF and MGIT culture results) and will only include individuals not on TB treatment at the time of enrolment. Estimation of sensitivity and specificity of Xpert MTB/RIF for the detection of rifampicin resistance against the reference standard of genotypic ± phenotypic DST on the culture isolate will be based on participants with *M. tuberculosis* detected by Xpert MTB/RIF and with a positive MGIT culture and valid drug susceptibility test (LPA ± phenotypic DST) results. This will include individuals on TB treatment at the time of enrolment (e.g. participants with AFB smear non-conversion or treatment failure).

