The evaluation of diagnostic accuracy is not the primary focus of the trial and the reference standard of a single culture could be considered an imperfect gold standard. In the initial Xpert MTB/RIF clinical validity studies, the reference standard used results of liquid and solid culture on two specimens (four culture results in total) [17]. Conversely, in the later demonstration studies, the reference standard varied between study sites and in some sites included results of only a single culture [18]. Observational data from the district in 2007 suggested that 5% of all culture-positive cases were multidrug-resistant [36]. Given that we will preferentially include suspects with a high risk of MDR-TB, we expect the overall proportion with MDR-TB to be at least 10%. It is possible that the impact of Xpert MTB/RIF positioning may be different for the drug-susceptible and drug-resistant cases. If this is the case then a higher or lower than expected proportion with MDR-TB could modify the effect of point-of-care placement, and this will be explored in secondary analyses.

There are a number of trials evaluating the impact of Xpert MTB/RIF in different settings and with different research hypotheses. Information about research projects is collated by the TREAT TB Xpert Research Mapping Project [37]. Several studies are examining point-of-care implementation but, to our knowledge, this is the only study directly comparing point-of-care use to centralised laboratory use. There is already some evidence from South Africa of the feasibility of implementation at the primary health care level, although several operational challenges were experienced when implemented within a very large urban clinic [38,39]. This study should provide direct evidence of any benefits of point-of-care positioning as well as further information about the costs and logistical challenges of such strategies. This can also be considered as a proof-of-principle study that will help to understand the benefits of bringing diagnostics closer to patients, and this will have broader relevance as we continue to develop and evaluate diagnostic technologies suitable for point-of-care use [40,41].

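### Rifampicin resistance, which is built into the primary outcome, is not prespecified as a covariate: the unadjusted analysis is valid but gives up some precision

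*Protocol article*

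**What the plan says.** All of this is in the protocol article; no statistical analysis plan is shown.

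- **Primary model** (Statistical analysis): "univariate logistic regression will be performed as the primary analysis using generalised estimating equations (GEE) with a binomial distribution function and a logit link".
- **Purpose of the baseline comparison** (same section): "to identify baseline imbalances between the study arms in order to decide whether any covariates need to be adjusted for in the final analyses".
- **Variables named for it**: "The baseline data will include: age, sex, body mass index (BMI), history of previous TB, HIV infection status, CD4+ cell count". The list ends with whether patients take ART or isoniazid prevention.
- **Covariate rule**: "important individual-level characteristics that are unbalanced between arms will be included in the model as covariates". It is introduced as an addition to the univariate analysis.
- **Role of resistance in the outcome**: Table 1 defines the appropriate initial regimen by the susceptibility pattern of the culture isolate.
- **Role of resistance in the pathway** (Implementation): the study nurse starts patients without rifampicin resistance on treatment. Those with rifampicin resistance are reported to the trial physician and "subsequently referred to the specialist drug-resistant TB treatment centre in Durban".
- **What is recorded at enrolment** (Implementation): "Demographic information, current symptoms, previous TB history, risk factors for drug resistance, HIV status, and history of ART use are documented".
- **What the Discussion expects**: an MDR-TB share of at least 10%, and that "a higher or lower than expected proportion with MDR-TB could modify the effect of point-of-care placement, and this will be explored in secondary analyses".

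**The concern.** Success on the primary outcome means starting the regimen that fits the isolate, within 30 days. Resistant cases need a different regimen and reach it through a distant referral centre, so resistance is likely to be among the strongest predictors of the outcome. It is absent from the variables named for choosing covariates. Of the MDR-TB risk categories listed under Participants, only previous TB is named.

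Two things are at stake. The first is precision: a strong predictor left out of the model leaves its variation in the error of the arm comparison. The second is prespecification. If resistance turns out unbalanced, adjusting for it would rest on a judgement of importance made after the data are seen, in a trial where the Discussion says patients and health care workers cannot be blinded.

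Resistance is a legitimate baseline covariate. Under Interventions, the culture specimen is taken on the day of enrolment and follows the same route in both arms. Table 1 cannot be scored without the susceptibility result, so no new data are needed.

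**Working it through.** **1. The plan's own sample size reproduces.** Inputs from Sample size: 85% v 95%, κ = 0.05, 12 cases per cluster, 80% power; two-sided 5% is taken from the stated 95% confidence.

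Hayes and Bennett: c = 1 + (1.96 + 0.84)² × [0.85×0.15/12 + 0.95×0.05/12 + 0.05²×(0.85² + 0.95²)] / 0.10² = 15.63, so 16 clusters per arm. Then 15.63 × 12 = 187.6, so 188 cases; 188/0.9 = 208.9 (stated 208); 2 × 208/0.25 = 1,664. Nothing below changes these figures.

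**2. Chance imbalance in resistant share.** With q the resistant share and n = 188 per arm, SD = √(2q(1−q)/n). This ignores any clustering of resistance by time block.

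- q = 10% (the Discussion's lower bound for MDR-TB): √(2×0.1×0.9/188) = 0.031, or 3.1 points; 95% range ±6.1 points.
- q = 5% (the Discussion's 2007 district figure): 2.25 points. This is relevant because the primary analysis excludes cases already on treatment.
- q = 15%: 3.7 points.

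**3. Effect on the risk difference.** Shift = imbalance × gap, where the gap is the difference in 30-day appropriate starts between susceptible and resistant cases. The documents give no gap, so a range is assumed. The planning SE of the risk difference is √(0.85×0.15/188 + 0.95×0.05/188 + 0.05²×(0.85² + 0.95²)/16) = 0.0344.

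| Assumed gap | 95% shift, q = 10% | Share of planning variance |
|---|---|---|
| 20 points | ±1.2 points | 3% |
| 40 points | ±2.4 points | 13% |
| 60 points | ±3.6 points | 29% |
| 80 points | ±4.85 points | 52% |

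At q = 5% the 95% shift runs from ±0.9 to ±3.5 points over the same gaps; at q = 15%, from ±1.4 to ±5.8.

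The upper rows need care. If the point-of-care arm truly reaches 95% with 10% resistant, the susceptible rate there is 0.95 + 0.1 × gap. That cannot exceed 1, so the gap in that arm is at most 50 points. A common 50-point gap gives 1.96 × 0.031 × 0.5 = ±3.0 points. Larger gaps in both arms fit only with lower overall rates, such as 85% in each.

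**4. Bias or random error.** In a simulation with no arm effect and 90% v 40% treated (susceptible v resistant, assumed), the unadjusted difference averaged 0.0 points. In the roughly 10% of trials with an imbalance of 5 points or more, it averaged about 3 points away from zero.

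**5. Power, arm only v arm plus resistance.** Simulated GEE: 16 clusters of 12 per arm, between-cluster coefficient of variation 0.05, independence working correlation, sandwich variance, t reference, 2,000 replicates, 85% v 95% intended overall. Starts among resistant cases are assumed.

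| Resistant share; resistant cases treated, laboratory to point of care | Arm only | With resistance |
|---|---|---|
| 10%; 75% to 85% | 76% | 77% |
| 10%; 55% to 72% | 73% | 76% |
| 10%; 40% to 68% | 74% | 79% |
| 10%; 25% to 55% | 69% | 79% |
| 15%; 40% to 75% | 72% | 76% |

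With no arm effect and 40% of resistant cases treated, type I error was 5.9% unadjusted and 5.3% adjusted.

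Only the gains should be read from this table. With overall rates fixed, arm-only power should hardly depend on how they split by resistance, yet it varies from 69% to 76%. A likely reason is that cluster effects pushing probabilities above 1 were cut off. A similar simulation with that truncation had the point-of-care rate at 93.5% to 94.1% instead of 95%. It still showed gains of 3 to 10 points.

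**The case against.** The strongest reply is that nothing here is invalid. An unadjusted primary analysis of a randomised comparison is sound, and its confidence interval already carries chance imbalance. That stands.

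Three stronger readings are tempting, and the document supports none of them.

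- **That leaving resistance off the list sends imbalance into the primary estimate.** The primary model is univariate, so imbalance in any factor, listed or not, stays in that estimate. Adding resistance to the list would alter only the additional adjusted model. The mean shift over randomisations is zero.
- **That the plan rules out adjusting for resistance.** The list is not worded as exhaustive, and the covariate rule speaks of important individual characteristics without confining them to the list. Previous TB, a partial proxy, is named. What remains is that importance is undefined and the choice follows observed balance.
- **That the Discussion concedes confounding by resistance.** It describes effect modification by the overall MDR-TB share, which is a different matter from imbalance between arms, and it promises secondary analyses. A main-effect term for resistance would not address effect modification. Those analyses would be imprecise: 10% of 188 to 208 cases is about 19 to 21 resistant cases per arm.

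It can also be said that covariates are often left to a statistical analysis plan, which may already name resistance. That is fair, and no finding is made of what that plan may contain. The point is confined to what the article does fix: a univariate primary model and a covariate choice driven by observed imbalance.

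**Conclusion.** The point holds as a low-cost improvement, not as an error that threatens validity. The plan forgoes precision on a factor that its own outcome definition and care pathway mark as probably strongly prognostic, and leaves adjustment for it to a post hoc choice.

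Its size depends on a quantity the documents do not give. With 188 cases per arm and 10% resistant, chance imbalance contributes about ±1.2 points to the risk difference (95% range) if the gap in 30-day starts is 20 points, and about ±4.9 if it is 80. If the point-of-care arm reaches its 95% target, a gap common to both arms cannot exceed 50 points, which is about ±3.0. Power gains run from about 1 point for a small gap to about 10 for the most extreme split tried, and 3 to 5 points in the cases between. The absolute power levels in those simulations should not be relied on. If resistant cases start treatment nearly as promptly as susceptible ones, little is gained, and the simulations showed no harm to type I error.

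**What to change.** - In the GEE model for the primary outcome, prespecify rifampicin resistance of the culture isolate (yes/no, from LPA/DST on the enrolment specimen) as a fixed covariate, whatever the observed balance.
- Add MDR-TB risk category, from the risk factors already recorded at enrolment, to the baseline table.
- Keep the unadjusted odds ratio as a sensitivity analysis.
- Report a standardised difference in proportions beside the adjusted odds ratio.

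The cost is a change of wording; no new data, visits or sample size are needed. The one drawback is that the odds ratio becomes conditional on resistance and is not directly comparable with the unadjusted one, which is why the standardised difference should accompany it.

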### Participants

Adult (≥18 years) pulmonary TB suspects with confirmed HIV infection and/or at high risk of MDR-TB are included after giving informed consent. These criteria were defined because of the high risk for mortality in these groups and prioritisation for Xpert MTB/RIF testing, in line with the WHO recommendations [20]. A TB suspect is defined for the purposes of the trial as an individual with a current cough (of any duration) with or without other symptoms. High risk of MDR-TB is defined according to national and international guidelines and incorporates the following categories: failure of the standard treatment regimen (2HRZE/4HR), failure of the re-treatment regimen (2HRZES/1HRZE/5HRE), acid-fast bacilli (AFB) smear non-conversion at month 2 or 3 of the standard or re-treatment regimen, relapse or return after default, any other previous TB (4 or more weeks of TB treatment), household contact with a known MDR-TB case, prison inmate within the last 12 months and health care worker [24,25]. Participants are excluded if they report a previous diagnosis of MDR-TB or extensively drug-resistant TB (XDR-TB), are severely unwell requiring admission to hospital, or are unable to give informed consent. Participants are recruited between the times of 0800 and 1630, Monday to Friday.

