### Outcome measures

The observational unit for all analyses is the individual participant. The primary outcome for the study is the proportion of culture-confirmed pulmonary TB cases initiated on appropriate TB treatment within 30 days of initial clinic visit (appropriate treatment defined according to results of LPA ± phenotypic DST on the culture isolate).

Secondary outcomes at an individual level are the following, with all time-to-event analyses using the initial clinic visit as time zero:

•All-cause mortality in TB suspects and MDR-TB suspects at 60 days

•Time to initiation of appropriate TB treatment (days) for culture-confirmed pulmonary TB cases

•Time to initiation of MDR-TB treatment (for MDR-TB cases confirmed by culture/LPA/DST)

•Proportion of TB suspects and MDR-TB suspects with at least one hospital attendance within 60 days

•Time to initiation of antiretroviral therapy (ART) for HIV-infected TB suspects and MDR-TB suspects not yet receiving but eligible for ART

•Sensitivity and specificity of Xpert MTB/RIF

▪ for *M. tuberculosis* detection (compared to reference standard of single MGIT culture)

▪ for detection of rifampicin resistance (compared to reference standard of phenotypic DST ± LPA)

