### Sample size

The study was designed to detect an increase from 85% to 95% in the proportion of culture-confirmed pulmonary TB cases initiated on appropriate treatment within 30 days. Sample size was calculated with the equation of Hayes and Bennett, using the coefficient of variation (κ) [26]. With κ = 0.05 and a cluster size of 12 culture-positive cases, we would need 16 clusters and 188 culture-positive TB cases in each arm to detect this difference with 95% confidence and 80% power. We assumed 10% of individual participants would be lost to follow-up at 60 days, so we would need 208 culture-positive TB cases in each arm. Based on the assumption that 25% of TB suspects would have a positive MGIT culture, we would require enrolment of 1,664 TB suspects. The total sample size will therefore be 32 clusters and 1,664 individual participants.

The coefficient of variation (κ) is small, but as the clusters are clinic time blocks rather than geographic areas or health care facilities, minimal variation is expected between clusters. This value of κ corresponds to a range of proportions appropriately treated within 30 days in the district hospital laboratory arm of 77-94%.

For the secondary endpoint of all-cause mortality within 60 days, the analysis will incorporate all participants (all suspects), regardless of presence or absence of TB disease. The sample size of 32 clusters and 60 participants per cluster gives approximately 80% power to detect a 33% reduction in mortality from 12% in the district hospital laboratory arm to 8% in the point-of-care arm, with 95% confidence.

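### The sample size makes no allowance for culture-positive cases already on TB treatment, whom the primary analysis excludes, so the stated 80% power is for a wider population than the one analysed

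*Protocol article*

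**What the plan says.** **Who can enrol.** The Participants section lists the categories that count as high risk of MDR-TB. They include failure of a treatment regimen and "acid-fast bacilli (AFB) smear non-conversion at month 2 or 3 of the standard or re-treatment regimen". Some enrolled suspects will therefore be taking TB treatment when they enter.

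**How the trial was sized.** The Sample size section works in culture-positive cases. The target is an increase from 85% to 95%. The inputs are given as "With κ = 0.05 and a cluster size of 12 culture-positive cases", and the result as "we would need 16 clusters and 188 culture-positive TB cases in each arm to detect this difference with 95% confidence and 80% power". Allowing for 10% loss to follow-up at 60 days raises 188 to 208 per arm. The last step is: "Based on the assumption that 25% of TB suspects would have a positive MGIT culture, we would require enrolment of 1,664 TB suspects".

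**Who is analysed.** The Outcome measures section defines the primary outcome as "the proportion of culture-confirmed pulmonary TB cases initiated on appropriate TB treatment within 30 days of initial clinic visit". The Statistical analysis section narrows this: "The primary analysis will include only TB cases not on TB treatment at the time of enrolment". It explains that the cases removed are smear non-converters and treatment failures still on treatment.

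**The group is foreseen.** The rifampicin-resistance accuracy analysis, which requires a positive MGIT culture, expressly includes participants on treatment at enrolment and gives the same two examples. No section states how many are expected.

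**The concern.** The chain from 188 to 208 to 1,664 has two conversion factors: 10% loss and 25% culture positivity. The second is applied to everyone enrolled. A third reduction, removal of culture-positive cases already on treatment, is planned in the analysis but absent from the chain. The stated power therefore belongs to a wider set of cases than the one that will be analysed.

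What is at stake is whether the 80% figure for the primary comparison can be relied on. Once the planned 10% has been lost, the design sits almost exactly at 80%, so even a small further exclusion takes it below that figure.

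**Working it through.** **Inputs.** All are from the Sample size section: p0 = 0.85, p1 = 0.95, κ = 0.05, m = 12 culture-positive cases per cluster, 16 clusters per arm, 80% power, 10% loss, 25% yield, 32 clusters and 1,664 participants. The 95% confidence is taken as a two-sided 5% test. The share f of culture-positive cases on treatment at enrolment is not given; values from 0 to 20% are assumed.

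**Step 1: reproduce the stated size.** The Hayes and Bennett formula for unmatched clusters is

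c = 1 + (1.96 + 0.84)² × [p0(1−p0)/m + p1(1−p1)/m + κ²(p0² + p1²)] / (p0 − p1)²

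- Binomial part: (0.1275 + 0.0475)/12 = 0.175/12 = 0.01458
- Between-cluster part: 0.0025 × (0.7225 + 0.9025) = 0.0025 × 1.625 = 0.00406
- c = 1 + 7.849 × 0.01865/0.01 = 15.63, so 16 clusters
- 15.63 × 12 = 187.6, so 188 cases per arm
- 188/0.9 = 208.9 (the article has 208)
- 208 × 2/0.25 = 1,664

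The stated figures reproduce.

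**Step 2: analysable cases per cluster.** 1,664/32 = 52 participants, and 52 × 0.25 = 13 culture-positive cases. After 10% loss this is 13 × 0.9 = 11.7 per cluster, or 187.2 per arm.

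**Step 3: power with the exclusion.** Solving the same formula for power with 16 clusters per arm gives

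Power = Φ( 0.10 / √{[0.175/n + 0.0025 × 1.625]/15} − 1.96 )

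with n = 11.7(1 − f) if the full 10% is lost, and n = 13(1 − f) if no primary outcome is lost. For n = 11.7, the bracket is 0.01496 + 0.00406 = 0.01902, the standard error is √(0.01902/15) = 0.0356, and power is Φ(2.808 − 1.96) = 80.2%.

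| Assumed share f on treatment | Cases per arm, 10% lost | Power, 10% lost | Cases per arm, none lost | Power, none lost |
|---|---|---|---|---|
| 0% | 187.2 | 80.2% | 208.0 | 83.3% |
| 5% | 177.8 | 78.6% | 197.6 | 81.8% |
| 10% | 168.5 | 76.8% | 187.2 | 80.2% |
| 15% | 159.1 | 74.9% | 176.8 | 78.4% |
| 20% | 149.8 | 72.8% | 166.4 | 76.4% |

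**Step 4: where power crosses 80%.** Power equals 80% at n = 11.63 per cluster (186.1 per arm). With the full 10% lost, that is f = 1 − 11.63/11.7, about 0.6%, or roughly one case per arm (187.2 − 186.1 = 1.1). With no outcome lost, it is f = 1 − 11.63/13, about 10.5%.

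**The case against.** A reader might infer that the trial will not deliver 80% power, or that any on-treatment case at all takes it below. The article does not support either reading. It never gives the on-treatment share. Only some of the listed MDR-risk categories involve current treatment, and confirmed HIV infection is a separate route into the trial, so the share could be small.

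The 10% loss is also set at 60 days, whereas the primary outcome is treatment initiation within 30 days. The Outcome evaluation section provides for telephone contact, home visits and, failing those, the clinic TB registers. A participant lost at 60 days may still have a known primary outcome, and power would then stay at or above 80% up to about 10.5% excluded. This stands, and it is why both columns are shown. The article does not, however, say that the loss allowance was meant to cover the exclusion.

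The yield is a round assumption. At 27%, with 7% excluded, 52 × 0.27 × 0.9 × 0.93 = 11.75 cases per cluster, which restores the margin. The mortality power statement uses 60 participants per cluster. That intake would give 60 × 0.25 × 0.9 = 13.5 cases and 84.3% power, staying at or above 80% until about 14% were excluded. But 60 conflicts with the 52 implied by 1,664/32, so it cannot be counted as spare capacity.

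A reader might also see two conflicting definitions of the primary outcome, because the abstract and the Outcome measures section omit the restriction. They are shorter statements in a condensed article, and the Statistical analysis section states the restriction openly and in advance. Repeating it elsewhere would be clarification only.

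**Conclusion.** The concern holds in this form: the sample size has no allowance for an exclusion that the plan itself specifies, and the 80% power refers to a wider population than the one analysed. The arithmetic as stated is sound.

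The size depends on two unknowns, the on-treatment share and how far the 10% loss affects the 30-day outcome. With the full loss, power is below 80% beyond about 0.6% excluded, and the shortfall stays within 2 points up to about 6.7%. With no loss, there is no shortfall up to about 10.5%. At an assumed 20%, power is 72.8% or 76.4% respectively.

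These figures assume a two-sided 5% test, κ = 0.05, 16 clusters per arm, 52 participants per cluster and a 25% yield that applies to everyone enrolled, as the text reads. If 25% was meant as the share of all enrolled who are culture-positive and untreated, the stated power already stands.

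**What to change.** Keep enrolment at 1,664. In the Sample size section, restate the primary-outcome power for the population analysed: culture-positive and not on TB treatment at enrolment. Use the on-treatment share observed among culture-positive participants, pooled over arms, and give power both with and without the 10% loss. State whether the 25% yield refers to untreated suspects or to everyone enrolled. If convenient, carry the restriction into the abstract and the Outcome measures section for clarity.

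The cost is one recalculation and a few sentences. It needs no outcome data by arm and changes neither conduct nor analysis. The downside is that the stated power may be slightly lower than 80%.
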